**Fig. 1 Fig1:**
[figure not shown]
Two-stage RCT design

In stage 2, following the month 4 assessment, those in iTAB-CV + SM will be re-randomized to receive either a high intensity (starts off with 1 reminder per day and tapers down to 1 reminder per week over the course of 2 months) or low intensity (1 reminder per week) booster. Adherence will be assessed by phone at month 5 as an interim measurement and an in-person assessment will occur at month 6. In stage 3, participants will be followed for another 6 months without intervention with one interim phone assessment and a final in-person assessment at month 12.

As this is a group of participants who may be particularly difficult to engage and retain in longitudinal research studies, there will be a number of measures taken to optimize retention. These include scheduling visits at maximally convenient times for participants, conducting visits remotely when possible, allowing for frequent breaks as needed during the procedures, hiring and training staff that will be flexible and attentive to the individual’s needs, and frequent opportunities for questions and feedback. Participants will also receive small items with the study logo of nominal monetary value but that will remind them of study participation such as a stress ball in the shape of a heart, pen to log adherence, and hand-sanitizer. Reminder calls will be made prior to assessments. Should there be challenges in meeting enrollment goals, the study team will request input from the SAB in additional procedures and processes that might optimize enrollment. Participants in all treatment groups will be compensated for assessments.

### Study setting

Research procedures will be performed either in the principal investigators’ (PIs) research offices, which are located at an urban academic medical center in Cleveland, Ohio, USA, or, given safety concerns in the COVID-19 era, can be conducted remotely. A list of study sites can be obtained by contacting the corresponding author. The consent process may be conducted using a secure videoconferencing system (Zoom) and via a secure data entry and storage system called Research Electronic Data Capture (REDCap). Other study procedures and visits may also be conducted via videoconferencing, phone, and/or via REDCap survey (individual link emailed directly to the participant) in the event an in-person visit is not possible. In addition, SAB meetings will be conducted remotely.

### Stakeholder advisory board (SAB)

To ensure that iTAB-CV meets the needs of patients and clinicians, and fits into workflows and operations of clinical systems, the investigators will obtain input from a SAB made up of patients, family members, clinical providers, and health system administration representatives. The SAB will meet for an hour approximately 3 times for the first 6 months of the project and then once yearly for a total of 7 meetings over the course of 5 years to (1) identify modest refinements of the intervention that will address barriers and facilitators to being able to implement the project and intervention in the RCT, (2) support recruitment/retention efforts, and (3) gather process data during the RCT regarding how future implementation and dissemination efforts might enhance reach and adoption of iTAB-CV into clinical settings. Information obtained from these local stakeholders will also help the investigators to develop a robust recruitment strategy and a set of practices that will maximize engagement and retention of participants.

The study team will collect demographic information from SAB members at the time of consent. Study staff will also collect information on SAB members’ lived or professional experience with BD/HTN and feedback on the program and implementation. SAB meetings will be audio/video recorded. Finally, after each meeting, study staff will survey SAB members on their satisfaction with the SAB meeting.

### Equipment and devices

All participants will receive a home BP monitor at screening and undergo training on its use by study staff based on a protocol provided by the British Hypertension Society (BHS) and the National Institute for Health Research [40]. They will also receive written information including a description and pictorial presentation of how to take and record BP readings. The monitors used in this study are the Omron® 3 Series BP7100 monitors and the Omron® 7 Series Wrist BP6350 monitors for those whose arms cannot fit a standard arm cuff (manufactured by Omron Corporation, Shimogyo-ku, Kyoto, Japan). Both models are validated and approved for home use [41], and both have a memory function to record and display several recent BP readings.

All participants will have remotely administered pill monitoring via the eCAP™ which records pill bottle openings to a secure, cloud-based database. Pill bottles equipped with eCAPs™ are capable of storing a 90-day supply of one medication. Once the eCAP™ is activated by the Certiscan® Secure Reader, the eCAPs™ record each time they are opened. The data are uploaded to the cloud remotely by scanning the eCAP™ via an app on the participant’s personal smartphone or by using the Certiscan® Secure Reader. The eCAP™ will be distributed to participants when they meet all inclusion criteria for enrollment. The measurement of adherence following the introduction of electronic pill monitoring has been shown to influence medication adherence (Hawthorne effect) initially [42]. In the pilot study, adherence improved in the 4 week period between screen and baseline. Therefore, the pre-intervention phase will be extended to 8 weeks during which both treatment arms will just be monitored via eCAP™. It is anticipated that 4 weeks is long enough for return to regular medication taking behavior, so the past month and past week adherence will be gathered from the second month. Participants are incentivized to return the eCAP™ at the end of their study participation.

### Educational video

Following baseline assessments and prior to randomization, all participants will watch a brief educational video about the symptoms, risks, and the important role of medication in the treatment of both HTN and BD. The content parallels that which was presented during the pilot delivered by the PI using a Powerpoint. The content was derived from publically available information disseminated by the American Heart Association on HTN [24] and by the National Institute of Mental Health on BD [43] and reviewed for accuracy and understandability by experts in internal medicine and psychiatry from the research team.

### Intervention

Individualized Texting for Adherence Building – Cardiovascular (iTAB-CV) for individuals with BD and HTN is an adherence intervention utilizing cognitive and behavioral principles based on a modified version of the Attitude-Social Influence-Efficacy theoretical model [44]. The iTAB-CV content aims to increase positive medication attitudes, draw on social support and comparison, and strengthen self-efficacy for medication taking behavior. Participants in the intervention group will receive texts that include educational/motivational content and be asked to respond whether the medication was taken. While the pilot presented iTAB-CV in 2 stages, the first with educational/motivational content but no reminders and the second with both educational content and reminders, participants indicated that they viewed the educational texts as reminders. As such, in the current trial, there will be no explicit medication reminders. The timing of the messages will correspond with their first antihypertensive medication dose of the day as determined by the participant and sent within a 1-h window (half hour before or after) of the scheduled time. The reason for the variability is to keep the system new and reduce the likelihood of ignoring messages that arrive at exactly the same time every day.

iTAB-CV texts will be administered for a total of 4 months. Participants in the intervention group will receive the texts once a day for 2 months following baseline, then following a second randomization of the iTAB-CV group, will receive the texts either once weekly or gradually tapered down from daily to once weekly for another 2 months.

In iTAB-CV, sending texts is automated via a central server, which provides an advantage over more labor intensive and costly approaches. The content of the iTAB-CV texting system messages combines predetermined content in 11 domains with customized message content. The order of the messages is prescheduled such that all participants will receive the same content on the same day of the study with placeholders for customized content. The customization ensures that texts are personal, salient, and do not become stale. The 11 domains were derived from the original focus groups conducted in phase I of the R21 and in consultation with the study co-authors with experience using the iTAB-CV system and clinical specialists [45]. The specific text stems were categorized into existing domains by 3 independent research staff (see Table 1).

**Table 1 Tab1:** Domains and sample stems

Domains	Sample stems
Hypertension knowledge	Blood pressure medication is a NECESSARY and EFFECTIVE way to lower blood pressure.
Bipolar disorder knowledge	BD^a^ results from a problem in the brain’s ability to regulate chemicals or ‘neurotransmitters’.
Benefits of blood pressure medication	Blood pressure meds help lower blood pressure and improves heart health.
Benefits of BD medication	BD meds help me function better and make it less likely that I will get depressed.
Making peace with medication	Although I may wish I did not need meds, accepting that I do makes me stronger!
Social support	My physical and mental health impacts others; I should take my meds for them.
Self-efficacy	I believe that if I take my meds daily, my health will improve.
Medication routines	Keep meds somewhere I will see them.
Spiritual	God grant me the serenity to take care of my health by taking my meds.
Self-esteem	I am special. I deserve to be healthy!
Social comparison	I would encourage others with BD to take medication to stabilize their mood.
Custom	Lisa wants me to be healthy so we can build a brighter future together!

^a^*BD* bipolar disorder

iTAB-CV is personalized with texts that are specific to the person, medication, and timing. Motivational interviewing demonstrates that change is more effective when patients use their own words to commit [45] and personalization of messages has been effective in changing behaviors in other diseases such as HIV-infected individuals with BD and in diabetes [46–48]. Moreover, iTAB-CV uses the participant’s own words for both reminders and reinforcers. Personalizing reminders and reinforcers offer an advantage over previous studies that have focused on medication timing and dosing but did not tailor the reminder itself [46–49]. Participants will be encouraged to write their own adherence reminders (e.g., I want to stay healthy so I can care for Sam and Jane for many years!”) as well as reinforcement stems within the character limits (e.g., “Susie is so proud of you for taking your meds!”). Participants will choose their preferred name for HTN and BD to be used in some of the text stems and will have the opportunity to opt out of 2 of 12 categories: Social Support and Spirituality. In those cases, Social Comparison texts, customized texts, and alternate texts will be substituted.

Adherence texts will be followed by a question asking whether medication was taken. All responses will be followed by immediate reinforcement either to reinforce medication taking behavior or to reinforce engagement with the system if response indicates medicine was not taken (see Fig. 2 for sample text and reinforcement exchange).

**Fig. 2 Fig2:**
[figure not shown]
Sample text messages

Participants in both treatment arms will receive mood rating messages from the iTAB-CV system once a week from baseline to the end of the study. They will be asked to rate how depressed they have felt on average (where 1 is “not at all” and 9 is “extremely” depressed) as well as how “up” or “irritable” they have felt on average (where 1 is “not at all” and 9 is “extremely” up or irritable) (see Fig. 3 for sample mood rating exchange). This method for collecting mood ratings was found to be feasible and acceptable in a study evaluating the use of text messaging for measuring change in depression over the course of a RCT [50]. Unlike in the pilot study where participants completed daily mood ratings, in this trial, we decided that more information regarding mood, including mixed symptoms, would be gained from two separate Likert scales and that weekly ratings would increase the message freshness and thus responsiveness. The automated system will also send all participants medication refill reminders for their antihypertensive medication once a month from baseline to the end of the study.

**Fig. 3 Fig3:**
[figure not shown]
Sample mood rating messages

Responses to texts and lack thereof will be recorded within the iTAB-CV system. Multiple responses to the same message will yield an automated text indicating that the message has already been received, and inaccurate responses (i.e., not in the requested format) will return an automatic message saying that a given text was not understood by the system. Similarly, there is an automated texting sequence to address lack of responsiveness. After 3 consecutive days of missed messages, the automated system will send an alert to a mobile interventionist (MI) for them to carry out follow-up phone calls to support troubleshooting. There is also a texting help email provided so the participant can correct any errors or solicit help from an MI.

### Mobile interventionists

Two MIs with at least a bachelor’s degree and experience working with individuals with serious mental illness and comorbid chronic medical conditions will be assigned to meet with participants based on MI and participant availability. The MIs will be trained and supervised by one of the PIs. The MIs will meet with participants between 30 and 60 min to personalize and train them on the use of the automated texting system. For individuals randomized to the intervention iTAB-CV + SM, MIs will use a structured interview, developed in the pilot study, targeting the 11 domains to identify what motivates them to take medications for HTN and BD, to personalize their adherence texts and reinforcers, and to determine whether they would like to opt in or out of the Spirituality and Social Support domains. The MI will also set up participants randomly assigned to SM in the system to receive their mood rating and refill reminder text messages. All participants will be trained on responding to the text messaging system by their assigned MI. To decrease potential bias, these interventionists will not be involved in the assessment component.

Participant and MI interview and iTAB-CV system setup for all participants will be video/audio recorded and a minimum of 25% of them will be viewed and assessed for fidelity by one of the co-PIs. The fidelity monitor will use a fidelity scale adapted from previous work using the iTAB-CV platform, discussing discrepancies and retraining mobile interventionists as needed. The fidelity monitor will also review at least 25% of the records to evaluate consistency between the structured interview set up form and the iTAB-CV system itself. The fidelity scale will be completed in its own REDCap project.

### Randomization

The study biostatistician will generate the allocation sequence and randomization lists will be computer-generated and integrated into a REDCap randomization project. Members of the study staff will not have access to the sequence prior to assignment. Stratified randomization will be employed to ensure that equal numbers of iTAB-CV + SM and SM patients are balanced with respect to sex and BD severity as reflected by BD type (type 1 vs type 2). The second randomization (high or low booster) will also be balanced with respect to sex and BD type. The MIs will randomize participants to an intervention at baseline using the REDCap project with pre-populated randomization criteria. The MIs will also conduct the second randomization of the iTAB-CV + SM group to booster, which is set up in the iTAB-CV texting system. RAs who complete assessments will be blind to condition by not having access to the randomization module or iTAB-CV system and administering assessments relevant to both arms regardless of assignment. Only the MIs are aware of randomization assignment and they do not carry out any assessments. While all efforts will be made to keep RAs blind to treatment condition, participants are not blinded to condition and thus could unintentionally reveal information to the RAs during an assessment or outreach by an RA in response to extreme moods. Given that this is not a drug trial and risk is low for both groups, there are no plans for intentional unblinding.

### Assessments and outcomes

Assessments for both iTAB-CV + SM and SM alone will include evaluation of medication treatment adherence, psychiatric symptoms, health status, self-efficacy for medication taking behavior, illness beliefs, medication attitudes, and habit strength for medication taking behavior. One-on-one assessments will be conducted at 5 time points over a 12-month time period. Adherence and BP will be measured at each of the 5 one-on-one assessments. There will be 3 additional remote/phone assessments which will collect adherence and BP data only. Individuals who drop out of the intervention, and who agree, will be followed up with outcomes assessments over the same 12-month time period that they would have been evaluated had they remained in the study.

Table 2 shows the variable constructs, how they will be measured, mode of data collection, and time points, following the structure of a SPIRIT figure. Demographic and clinical variables measured at baseline will include age, sex, race/ethnicity, education, marital status, and health status. Assessment visits include one-on-one screening, baseline (2 months), V1 (3 months; by phone), V2 (4 months), V3 (5 months; by phone), V4 (6 months), V5 (9 months; by phone), and V6 (12 months). All assessments will be done by a RA trained by the PIs with pre-established and documented reliability standards. Training will use video clips of non-study volunteers or actors. It is expected that patient assessment will require approximately 90 min for the screening assessment and approximately 60 min for the follow-up assessments. Study visits designated as one-on-one may take place in person, via phone or via video conferencing as needed.

**Table 2 Tab2:** Study instruments and assessments schedule

Construct	Measurement	Mode	Screen	BL	V1 phone	V2	V3 phone	V4	V5 phone	V6
**Primary outcomes**										
Blood pressure	Systolic blood pressure	REDCap	X	X	X	X	X	X	X	X
Antihypertensive adherence	TRQ	REDCap	X	X	X	X	X	X	X	X
	eCAP™			X	X	X	X	X	X	X
**Secondary outcomes**										
Mood stabilizer adherence	TRQ	REDCap	X	X	X	X	X	X	X	X
Psychiatric symptoms	BPRS	REDCap		X		X		X		X
	MADRS	REDCap	X	X		X		X		X
Self-efficacy for medication taking	MASES-R	REDCap		X		X		X		X
Medication attitudes	BMQ	REDCap		X		X		X		X
	AMSQ	REDCap		X		X		X		X
Habit strength	SRHI	REDCap		X		X		X		X

*BL* baseline

V1 = 3 months

V2 = 4 months

V3 = 5 months

V4 = 6 months

V5 = 9 months

V6 = 12 months

The primary outcomes are SBP and adherence with antihypertensive medication. While SBP is the primary outcome for this analysis, both SBP and diastolic BP will be measured. A recently published joint Policy Statement from the AHA and American Medical Association recommend home-based BP monitoring for the most accurate assessment to minimize biased/artifact findings and yield the most valid results [51]. The joint statement states, “BP may differ considerably when measured in the office and when measured outside of the office setting, and higher out-of-office BP is associated with increased CV risk independent of office BP. Self-measured BP monitoring, the measurement of BP by an individual outside of the office at home, is a validated approach for out-of-office BP measurement. Several national and international HTN guidelines endorse self-measured BP monitoring.” In addition to optimizing accuracy, use of home-based BP evaluation will minimize potential COVID-19 exposure for study participants, most of whom are adults with multiple chronic health conditions.

At screening, participants will be trained on the use of the BP monitor following the BHS protocol [40]. Participants will be asked to take their own BP 2 times consecutively with 1 minute in between each reading and after sitting in a chair quietly for 5 min. BP readings will be collected twice a day, in the morning and evening, for 3 to 7 days while a member of the study staff observes the participant over a video platform, in person, or over the phone. Alternately, the participant can send a screen shot of the BP readings via text to study staff. Once they have obtained 12 readings total (6 in the AM and 6 in the PM), SBP will be averaged across all readings. Participants will also use these procedures to ascertain BP readings at follow-up time points. The interim BP readings will be conducted in real-time using the remote platform or by phone in real time, or if needed, will be measured beforehand and reported during the visit.

Antihypertensive medication adherence will be evaluated with the self-reported Tablets Routine Questionnaire (TRQ) [52, 53] for the past week and the past month. Self-reported adherence will be validated with the eCAP™. While the literature on measurement of adherence including the co-PIs’ own work in this area acknowledges limitations for all methods of adherence assessment, both self-report and automated pill-caps appear valid and practical for use in BD studies [21, 54].

At screening, participants will be asked about their demographic information and current medication taking behaviors to determine if they meet inclusion criteria. Participants will also undergo a diagnostic interview based on the DSM and ICD psychiatric disorders called the Mini-International Neuropsychiatric Interview (MINI) [55] to confirm BD diagnosis and assess for suicidality. Data on comorbid medical conditions will be collected based on the self-report version of the Charlson Comorbidity Index (CCI) [56]. While the original CCI includes dementia, it was excluded from the self-report version given that those with dementia would not be able to provide informed consent. Finally, participants will be administered the Rapid Estimate of Adult Literacy in Medicine-Revised (REALM-R) [57] to assess health literacy.

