### Sample size calculations

Power analyses are based on computations from the Repeated Measures and Sample Size (RMASS) [72] with inputs estimated from prior study data. Our projected sample size is *n* = 200, with 100 participants per arm. In this power analysis, the research team will assume type I error levels of 0.025 for each of the two primary analyses, using Bonferroni correction to account for multiple comparisons. Conservatively, for this study, the researchers will assume 25% attrition based on a previous 12 month trial conducted by members of the study team with individuals with comorbid serious mental illness and diabetes [73]. For sample size requirement for aim 1, the investigators used past-month TRQ as an approximation of expected and longer-term maintenance adherence status and considered primary outcomes to be at 3 months. The investigators expect similar or even greater effect sizes at 4 months given the longer treatment duration. In the pilot study, there was 23.10% improvement in TRQ observed for iTAB-CV. The control comparator for the efficacy trial will be SM of adherence, BP, and mood. Based on the literature, no improvement in self-reported adherence was reported in a similar control arm [74]. The study staff thus assume no change in adherence. In a BD adherence RCT, 7% improvement was observed in the control arm. Hence, the investigators conservatively project a 7% mean improvement in adherence among controls. Thus, (1) there is a mean difference of 16.1% in adherence after 4 months between arms and (2) suppose autoregressive (AR(1)) model covariance structure with correlation coefficient of 0.44 and an error variance of 308, as estimated value from the data. With assumed attrition of 25%, for a 2-sided test of the treatment by time interaction effect being equal to zero, and with alpha = 0.025 and power = 0.80, the required total sample size is approximately 78.

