From the pilot data, mean screen SBP was 144.81 (SD 15.46). Change from screen to 3 months with the iTAB-CV intervention saw a mean reduction in SBP of 8.78. Reductions in BP of at least 2 mmHg can significantly reduce the incidence of cardiovascular disease and its complications in both hypertensive and normotensive individuals, and reductions of the magnitude seen in this team’s pilot work is well above thresholds that are considered clinically meaningful [75]. Based on our preliminary mixed model, the researchers also observed compound symmetry correlation parameter value of 0.36. This covariance model had similar model fit as with an AR(1) model in terms of AIC/BIC criteria and parameter estimate values. The researchers will assume no SBP pressure change is observed in the SM arm and estimated error standard deviation of 15.46, as observed [38]. Finally, in a linear mixed model with participant-level random effects, with two-sided type I error of 0.025, power = 0.80 for the projected sample size of 182 participants. The study staff will target a sample of 200 for the study to allow for some deviation from assumptions. Thus, the researchers should have sufficient statistical power for the first 2 primary aims.

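### SBP readings that staff cannot see (phone-observed at any visit, or reported at an interim visit) enter the outcome with no required photo or memory check

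*Protocol article*

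**What the plan says.** SBP is one of two primary outcomes. It is measured at home by the participant and averaged over 12 readings (Protocol article, Assessments and outcomes, text after Table 2). Several routes to the recorded value are accepted:

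- Staff observe the participant by video, in person or by phone. The same procedure applies at follow-up, and the section also lets one-on-one visits be held by phone.
- "Alternately, the participant can send a screen shot of the BP readings via text to study staff".
- Interim readings are taken in real time on the remote platform or by phone, "or if needed, will be measured beforehand and reported during the visit".

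The Equipment and devices section says of the two monitor models that "both have a memory function to record and display several recent BP readings". The Randomization section says that "participants are not blinded to condition". The primary SBP model runs to V2 at 4 months (Data analysis plan).

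**The concern.** On a voice call staff cannot see the display, and a value measured before an interim visit is not observed at all. In both cases the number in REDCap is what the participant says it is. The section does not require a screenshot or memory read-out for these readings, although both means are at hand.

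Participants know their arm, and only the iTAB-CV arm receives adherence texts with reinforcement of replies. Rounding or favourable choice of readings could therefore differ by arm after randomization. Blinding the research assistants does not protect a value that the participant supplies. At stake is how far the SBP result can be read as an objective measurement. The article does not say that the capture mode is recorded; if it is not, the size of any such effect could not be judged afterwards.

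**Working it through.** **1. Which values can be unseen, and where they enter**

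| Visit | Month | Route staff cannot see | Role |
|---|---|---|---|
| Baseline | 2 | phone observation | precedes randomization, so no arm-differential error |
| V1 | 3 | phone observation; reported fallback | inside the primary window |
| V2 | 4 | phone observation | end of the primary window |
| V3 | 5 | phone observation; reported fallback | after the primary window |
| V4, V6 | 6, 12 | phone observation | secondary contrasts |
| V5 | 9 | phone observation; reported fallback | only visit for the 9-month comparison named under Objectives |

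**2. The plan's own figure**

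Inputs (Sample size calculations): "type I error levels of 0.025 for each of the two primary analyses"; a "mean reduction in SBP of 8.78" mmHg under iTAB-CV; "no SBP pressure change is observed in the SM arm"; error SD 15.46; compound symmetry correlation 0.36; attrition 25%. The stated result is "with two-sided type I error of 0.025, power = 0.80 for the projected sample size of 182 participants".

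- SD of change = 15.46 × √(2 × (1 − 0.36)) = 17.49.
- Total N without attrition = 4 × 17.49² × (2.241 + 0.842)² / 8.78² = 150.9.
- Mixed model on baseline, V1 and V2, linear time, attrition building linearly to 25% at V2 (assumed; the pattern is not stated): 182.5.

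This matches 182, so the same set-up serves for the next steps. No figure in the plan is disputed.

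**3. Weight of each visit in the primary contrast (linear time)**

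- Complete data: the weights for the 2-month change are −1, 0 and +1 for baseline, V1 and V2.
- Attrition building to 25%: −1.05, +0.09 and +0.95.

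A 5 mmHg arm-differential error in every V1 value would thus move the estimate by about 0.09 × 5 ≈ 0.5 mmHg. If it affected 25% of iTAB-CV values at V1, the shift would be about 0.09 × 1.25 ≈ 0.1 mmHg. V2 carries nearly the full weight.

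**4. Error at V2**

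The documents give neither the share of unseen values nor the size of any misreporting, so both are assumptions. Bias = share of iTAB-CV values affected × under-report. Take 100 × (1 − 0.25) = 75 completers per arm and compare change from baseline: SE = 17.49 × √(2/75) = 2.86. With no true effect, type I error = P(Z > 2.241 − bias/SE) + P(Z < −2.241 − bias/SE).

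| Share affected | Under-report (mmHg) | Bias (mmHg) | Share of 8.78 | Type I error (planned 0.025) |
|---|---|---|---|---|
| 10% | 2 | 0.2 | 2% | 0.025 |
| 10% | 5 | 0.5 | 6% | 0.027 |
| 25% | 2 | 0.5 | 6% | 0.027 |
| 25% | 5 | 1.25 | 14% | 0.039 |

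**5. Room for selection**

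Two readings, twice a day, for 3 to 7 days give 12 to 28 readings, and 12 are needed. A longer collection period leaves some choice over which are passed on, although the text says that all readings are averaged.

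**6. V5**

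No other visit measures SBP at 9 months. In a discrete-time comparison at that visit, an error there passes into the estimate in full (25% at 5 mmHg gives 1.25 mmHg).

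**The case against.** The fallback at interim visits is limited: real time is the default, it covers V1, V3 and V5 only, and V1 barely enters the linear-time contrast. This stands, and it is why the concern for the primary analysis rests on phone-observed V2 values instead. V1 could count for more if time is categorical and the interaction is tested jointly, an alternative that the Data analysis plan leaves open.

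The arm-differential mechanism is plausible but not shown. Both arms watch the same video and both monitor their blood pressure; 12 readings are required, and averaging is over all of them. Oral reporting is an inference from a phone visit. These points limit the likely size but do not supply a check on the value.

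Home measurement is a reasoned choice, defended on accuracy and on COVID-19 exposure. That stands, and nothing here argues against it.

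A capture-mode field and a sensitivity analysis are commonly left to the full protocol or the SAP, so their absence from an article is no fault. What remains is that the article itself states which routes are accepted, and two of them leave staff without sight of the reading.

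A reader might go further and infer that both primary outcomes share one unchecked reporting bias. The documents do not support this: self-reported adherence is validated against the eCAP pill monitor, with correlation and Bland-Altman comparison planned.

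**Conclusion.** The point holds in limited form. Some post-randomization SBP values, including those at V2, can enter the data with neither a visual nor a stored check, in a trial whose participants know their arm. It would be wrong to infer that the primary SBP outcome is in general self-report: video, in-person and screenshot routes all exist, and the unobserved route is a fallback confined to interim visits.

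The size is unknown. Under the assumptions shown, bias at V2 ranges from a negligible 0.2 mmHg to 1.25 mmHg, the latter raising type I error from 0.025 to about 0.039. Through V1 alone it is a small fraction of that under linear time; at V5 it would pass through in full. The change is an inexpensive improvement to a stated procedure for a primary outcome. The finding does not invalidate the design.

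**What to change.** Keep home measurement and all existing visit modes. For every SBP reading that staff do not see on video or in person, require a texted photo of the display or memory screen. Ask for it at each measurement session: the article says only that recent readings are displayed, and does not show that the memory holds all 12.

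Record in REDCap whether each value was seen or photographed, or reported only. Keep reported-only values where no photo is possible, so that the rule does not create missing data. Repeat the primary SBP model without them as a pre-specified sensitivity analysis. It should stay a sensitivity analysis, because capture mode is determined after randomization.

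Cost: a sentence in the visit procedure, one REDCap field and one extra model run. All participants must already have a phone that can text. The downside is a small added burden on participants, and some values will remain reported-only.
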